## Abstract

**Introduction:**

Supervised community treatment (SCT) for people with serious mental disorders has become accepted practice in many countries around the world. In England, SCT was adopted in 2008 in the form of community treatment orders (CTOs). CTOs have been used more than expected, with significant variations between people and places. There is conflicting evidence about the effectiveness of SCT; studies based on randomised controlled trials (RCTs) have suggested few positive impacts, while those employing observational designs have been more favourable. Robust population-based studies are needed, because of the ethical challenges of undertaking further RCTs and because variation across previous studies may reflect the effects of sociospatial context on SCT outcomes. We aim to examine spatial and temporal variation in the use, effectiveness and cost of CTOs in England through the analysis of routine administrative data.

**Methods and analysis:**

Four years of data from the Mental Health Services Dataset (MHSDS) will be analysed using multilevel models. Models based on all patients eligible for CTOs will be used to explore variation in their use. A subset of CTO-eligible patients comprising a treatment group (CTO patients) and a matched control group (non-CTO patients) will be used to examine variation in the association between CTO use and study outcomes. Primary outcome will be total time in hospital. Secondary outcomes will include time to first readmission and mortality. Outputs from these models will be used to populate predictive models of healthcare resource use.

**Ethics and dissemination:**

Ethical approval has been granted by the National Health Service Data Access and Advisory Group and Warwick University. To ensure patient confidentiality and to meet data governance requirements, analyses will be carried out in a secure microdata laboratory using de-identified data. Study findings will be disseminated through academic channels and shared with mental health policy-makers and other stakeholders.

Strengths and limitations of this studyThis will be the largest and most complete study of its kind and the national representativeness of the study sample, deriving from routine clinical activity, is a major strength.The study design reflects the range of real-world settings in which mental health services are delivered and patients live in England.The use of multilevel models will allow us to estimate variation in community treatment order (CTO) use and outcome at individual, area and service level and to establish who CTOs work for and in what circumstances.Study limitations include confounding by indication and bias arising from missing data within the routine administrative data source.

## Introduction

Community treatment orders (CTOs), a form of supervised community treatment (SCT), were introduced to the Mental Health Act (2007) (MHA) in England and Wales in 2008 and allow certain patients detained in hospital to continue treatment in the community following discharge under specific conditions. To be eligible for a CTO, a patient must be detained in hospital under the MHA on a section that allows for compulsory treatment. The most common inpatient treatment orders are sections 3 and 37, the former being a civil order and the latter a forensic, court-imposed equivalent for mentally ill offenders. A CTO provides the clinical team the power to recall the patient to hospital after discharge.

At CTO initiation (the point of discharge from inpatient care), there are two mandatory conditions, namely that the person subject to a CTO makes themselves available for assessment for its renewal and (where necessary) to be seen by an approved second opinion doctor (SOAD) for the purposes of assessing proposed treatment plan should the patient lack capacity in respect of their treatment. Discretionary conditions can also be specified which most often include treatment (ie, medication) adherence and engagement with services (eg, attending for appointments with professionals). CTOs do not permit compulsory (ie, forcible) treatment in the community,^1^ but those who default from these conditions may be recalled to hospital for assessment if there are grounds to suspect deterioration in their mental health and/or risk to the patient or others. Where this assessment indicates the need for further treatment, the CTO is revoked and the original treatment order applies.

There were two motivations for introducing CTOs in England and Wales^2^: to reduce ‘revolving door’ admissions associated with non-adherence with care by a small group of patients, and to allow treatment in the least restrictive setting, in accordance with the Human Rights Act (1988). While it was originally envisaged that around 10% of eligible patients would be placed on CTOs, the figure is currently closer to 30%.^3^ Since more CTOs are issued than are ended each year, the number of patients subject to CTOs has increased over time. Almost five thousand CTOs were issued in 2016–2017, with use varying between demographic groups: rates of CTO use for males (11.4 per 100 000 population) were almost twice the rate for females (6.6 per 100 000 population), and the rate for black and black British people (60.1 per 100 000 population) was almost nine times the rate for those of white ethnicity (6.8 per 100 000 population).^4^ Use also varies between National Health Service (NHS) (provider) Trusts.^5 6^

SCT has been adopted in over 75 other jurisdictions around the world,^7^ although it is used differently in different places. This is highlighted by its different names, including ‘involuntary outpatient commitment’, ‘assisted outpatient treatment’, ‘supervised discharge’, ‘compulsory community treatment’ and ‘compulsory ambulatory treatment’.^8^ In some places, SCT is initiated only by courts, while elsewhere, as in England, it remains a matter exclusively for health and social care providers, although within a framework prescribed by statute and subject to legal review. There are also differences between countries in the organisation and funding of mental health services, including separation of inpatient from community mental health teams and variations in the nature and availability of care for people with severe mental illness. Generalising findings between countries is therefore problematic.

Despite widespread use, SCT remains controversial. In part, this is because patients and carers see it as coercive, raising fears of negative effects on therapeutic relationships.^9^ This disquiet has been heightened by conflicting research evidence about effectiveness.^10^ There have been only three randomised controlled trials of CTOs, two in the USA and one in the UK. None demonstrated significant benefit of CTOs in terms of hospital readmission, social functioning, quality of life, mental state or offending.^11–13^ Randomised trials of CTOs face particular ethical and practical challenges (including relatively brief duration of follow-up), and these limit their utility.^14^ In critically appraising the two US trials, Kisely *et al* highlighted small sample sizes, the court-imposed nature of compulsory community treatment and the exclusion of patients with a history of violence. The OCTET trial in England experienced several methodological limitations, including the involuntary nature of the control condition, high rates of non-participation and patients who moved between trial arms after randomisation.^15–17^

Apart from the inevitable unblinding of participants and clinicians, it is impossible to disentangle the effects of legal compulsion from the vigilance and intensive care associated with CTO implementation.^8^ Further trials of CTOs are unlikely, given ethical challenges inherent in randomising those who may lack insight, and who may be dangerous to themselves or others, to legal restriction versus truly voluntary care.^18^

The results of observational studies are less consistent, with some showing decreased admission rates and reduced bed use among those subject to SCT, while others do not.^2 8 10 14 19^ After excluding uncontrolled studies, observational research is characterised by matched cohort designs and before and after studies, with outcomes generally (but not invariably) assessed over 2 years or less. More recently, findings have emerged which suggest that patients on CTOs may experience better physical health and reduced mortality.^20 21^

Population-based observational studies using routine clinical and administrative data allow analysis of variation in SCT use and outcome to be studied.^10 22^ We will use 4 years of data from the Mental Health Services Dataset (MHSDS) to address the following aims: (1) to examine spatial and temporal variation in the use of CTOs; (2) to estimate associations between CTO use and patient outcomes; (3) to explore variation in these associations between patients, places and providers, establishing when, where and for whom CTOs may be effective and (4) to estimate the financial costs and benefits associated with CTOs.

## Methods and analysis

### Data sources and study outcomes

The use of CTOs in England is recorded as part of a mandatory administrative dataset, the MHSDS, formerly known as the Mental Health Minimum Dataset, and then the Mental Health and Learning Disabilities Dataset.^23^ MHSDS collates monthly returns from health service providers on all patients in contact with secondary mental health services provided and/or funded by NHS England. This includes voluntary and involuntary inpatient treatment, outpatient attendance, day treatment and other episodes of secondary mental healthcare.

MHSDS data are based on spells of care for individual patients. Since 2011, the dates on which specific care spells start and end have been included. Care spell dates can therefore be used to determine duration of CTO use and hospital (re)admissions. Four years of MHSDS data will be used covering the period 2011/2012 to 2014/2015, hereafter referred to as the study period. MHSDS records contain a unique patient identifier code which will be used to link patient care spells across the study period. This identifier will also be used to link patient records to the Office for National Statistics (ONS) Mortality Database, to ascertain patient deaths. Access to and linkage of, these different administrative data sets will be facilitated by the ESRC Administrative Data Research Network.

### Covariates

MHSDS provides data on a range of patient characteristics, including age, sex and ethnicity. Data on clinical characteristics are also available such as diagnosis, care clusters (groupings of patients with similar needs and problem severities)^24^ and Health of the Nation Outcome Scales (outcome ratings for a range of health and social domains).^25^ Additional patient characteristics such as marital, employment and accommodation status may be present in the dataset, although previous research noted high levels of missing data.^26^

MHSDS patient records also include several spatial/service setting identifiers (table 1). These will be used to link patient records to data on factors shown by previous studies to influence mental health outcomes at local area and service provider level. Specifically, English Indices of Deprivation 2015 will provide information about local area socioeconomic characteristics while ONS 2011 Census data will be used to characterise local populations, including through the use of population density and ethnic composition data.^27 28^

**Table 1 T1:** Spatial/service setting identifiers present in the Mental Health Services Dataset

Spatial/service setting identifier	Description
Lower layer super output area	Local area of residence, based on 2001 Census boundaries, typically containing 672 households and 1614 residents
General practitioner practice	Primary care provider
National Health Service and independent sector provider trust	Provider of secondary mental healthcare
Primary care trust	Commissioner of secondary mental healthcare

### Data analysis

As the overarching aim of the study is to examine spatial and temporal variation in CTO use and outcome, multilevel models (MMs) will be used.^29^ MMs allow variation in outcomes to be apportioned to the appropriate spatial level (eg, between patients, local areas and service settings) as well as estimating associations with individual, area and service-level characteristics.^30^ Since the local areas that patients live in do not nest hierarchically within the health service settings where they receive care (and vice versa), cross-classified MMs (CCMMs) will be used (figure 1).^31^

**Figure 1 F1:**
[figure not shown]
An illustration of cross-classified multilevel data.

Analysis will be conducted in three stages. First, CCMMs based on all patients eligible for CTOs will be used to explore spatial and temporal variation in the use of CTOs. CTO use will be considered as a binary outcome (patients subject to a CTO during the study period vs those who were not) and analyses will be undertaken using logistic multilevel regression. Models will estimate the variation at each level in the risk of being on a CTO and assess the extent to which any variation in this outcome is associated with patient, local area and health service characteristics. We will also investigate the duration of time spent subject to CTO (in days). Poisson/negative binomial link function CCMMs will be used and will include offset variables to take account of different observation times for patients.^32^

Next, to examine associations between CTO use and a range of outcomes, a cohort of patients will be constructed consisting of a treatment group (those who have been on a CTO) and a matched control group (those who are eligible but who have not been on a CTO). To prevent bias arising from secular changes in clinical practice, we will frequency match these groups according to the start date of the CTO (CTO group) and the end date of the CTO-eligible section of the MHA (non-CTO group), with tolerance limits determined after inspection of the data. As these dates are the point within the study period at which patients in both treatment groups are discharged from hospital, they represent the index date for each arm of the study. Models based on the cohort of matched patients will be used to test associations between SCT use and patient outcomes: total time spent in hospital, time to first readmission and mortality. For total time spent in hospital, count models based on Poisson or negative binomial distributions will be estimated. For time to first readmission, discrete-time survival analysis models will be estimated. For mortality, binary response models based on the logistic distribution will be estimated. To control for confounding by indication, we will adjust analyses for the propensity of being placed on SCT,^33^ with propensity scores being modelled using the pool of available variables which will include age, sex, ethnicity, diagnosis and previous admissions (where known). CCMMs based on this cohort will be used to test for the overall ‘average’ effect of CTO on each of the study outcomes. The models will also assess whether there is significant spatial and temporal variation around these average effects and estimate the extent to which this is associated with patient, local area and health service characteristics, including the length of time that patients are on CTOs.

Finally, we will use outputs from our CCMMs to populate predictive models of healthcare resource use incorporating the predicted impact of CTOs. We will model differences in treatments costs (eg, bed days and number of contacts with mental health staff) between patients who are and are not on CTOs. We will also quantify the administrative burden of CTOs, using protocols for mandated governance processes (eg, Mental Health Act Review Tribunals and SOADs) that apply to the use of CTOs. Projected costs associated with different plausible future trajectories of CTO use will be calculated and a probabilistic sensitivity analysis will be presented for each projection based on estimates of parameter uncertainty derived from the CCMMs.

CCMMs will be estimated in MLwIN using Markov chain Monte-Carlo (MCMC) Bayesian methods.^34^ This approach is suited to the complexity of the MHSDS and will provide unbiased measures of variation in CTO use and outcome, and associations with patient, local area and health setting characteristics. MCMC modelling diagnostics, together with measures of multilevel variation, will be used to evaluate different models to quantify where, and for whom, associations and variation occurs.^35–37^

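### The stage 1 model of CTO use scores eligible patients never discharged in the window as non-users, so differences in length of detention can appear as differences in CTO use

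*Protocol article*

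**What the plan says.** The Introduction of the Protocol article defines eligibility as a detention status: "To be eligible for a CTO, a patient must be detained in hospital under the MHA on a section that allows for compulsory treatment". It adds that "The most common inpatient treatment orders are sections 3 and 37", so both civil and forensic detentions qualify. It ties the start of a CTO to leaving hospital: "At CTO initiation (the point of discharge from inpatient care".

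Under Methods and analysis, Data analysis, the first stage is described thus: "CCMMs based on all patients eligible for CTOs will be used to explore spatial and temporal variation in the use of CTOs". The outcome is binary, "patients subject to a CTO during the study period vs those who were not", and "analyses will be undertaken using logistic multilevel regression". The next model, for days spent on a CTO, is a count model that "will include offset variables to take account of different observation times for patients". No such allowance is stated for the logistic model of use.

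The window is fixed: "Four years of MHSDS data will be used covering the period 2011/2012 to 2014/2015". For the second stage only, both groups are anchored on a discharge inside the window: the start of the CTO, or the end of the CTO-eligible section for controls.

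**The concern.** Eligibility begins with detention, but a CTO can begin only when that detention ends in discharge. Suppose a patient is detained on a qualifying section and is still detained when the window closes, or dies in hospital first. That patient is in the stage 1 denominator and, unless on a CTO carried over from before the window, is coded as a non-user. No discharge occurred at which a CTO could have been chosen, so censored or competing outcomes are counted as decisions against a CTO.

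Stage 1 exists to estimate variation in CTO use between patients, areas and services, and over time. If providers differ in the share of eligible patients who reach discharge, that difference enters the provider-level variance. If case-mix groups differ (section 37 against section 3, for example), it enters their coefficients. If time is represented by year of admission, recent admissions have had less time to reach discharge, and use appears to fall.

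**Working it through.** The article gives no stage 1 rate, length of stay or undischarged share, so there is no figure of its own to reproduce. What follows is an illustration.

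**Inputs**
- Window T = 48 months (four years, from Data sources and study outcomes).
- Probability of a CTO at discharge p = 30%, the same at every provider. This is an assumption. The Introduction's figure of about 30% is a share of eligible patients, not of discharges.
- Share of eligible patients with no discharge in the window, u. This is an assumption.

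**Formula.** Apparent use = p × (1 − u), with one detention per patient and no carried-over CTOs.

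**Two providers with identical practice, u = 5% v 20%**
- Apparent use: 0.30 × 0.95 = 28.5%, and 0.30 × 0.80 = 24.0%.
- Odds: 0.285/0.715 = 0.399, and 0.240/0.760 = 0.316.
- Odds ratio: 0.399/0.316 = 1.26, where the true value is 1.00.
- The ratio of proportions is 0.95/0.80 = 1.19 whatever p is. With p = 10%, the share the Introduction says was first envisaged, the odds ratio is (0.095/0.905)/(0.080/0.920) = 1.21.

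**Linking u to length of stay.** Assume exponential stays with mean m months.
- Admissions spread evenly over the window: u = (m/T)(1 − exp(−T/m)).
- Steady state, including patients already detained at the start: u = m/(m + T).

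Odds ratios below are against a provider that discharges everyone (use 30%, odds 0.429).

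| Mean stay m (months) | u, even admissions | Apparent use | Odds ratio | u, steady state | Apparent use | Odds ratio |
|---|---|---|---|---|---|---|
| 3 | 6.2% | 28.1% | 0.91 | 5.9% | 28.2% | 0.92 |
| 6 | 12.5% | 26.3% | 0.83 | 11.1% | 26.7% | 0.85 |
| 12 | 24.5% | 22.6% | 0.68 | 20.0% | 24.0% | 0.74 |
| 24 | 43.2% | 17.0% | 0.48 | 33.3% | 20.0% | 0.58 |

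Solving the steady-state formula for m gives m = uT/(1 − u). So u = 5% corresponds to a mean stay of 0.05 × 48/0.95 = 2.5 months, and u = 20% to 0.20 × 48/0.80 = 12 months.

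**Admission year.** For admissions spread over a year, with between a and a + 12 months left in the window, u = (m/12)(exp(−a/m) − exp(−(a + 12)/m)). With m = 6 and a = 36, 24, 12 and 0, apparent use by year of admission is 30.0%, 29.8%, 28.2% and 17.0%, although practice is constant.

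**After restriction.** Among patients discharged in the window, apparent use is p = 30% at every provider and the odds ratio is 1.00, provided the choice at discharge does not depend on length of stay.

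**The case against.** The strongest reply is that the denominator is inferred. The Introduction summarises the law, the stage 1 text does not say whether discharge is required, and a condensed article may leave the rule to a fuller protocol. A narrower definition may indeed exist there. But the only definition of eligibility in the article is by detention, and its discharge anchor is stated for the matched cohort alone. The article also recognises unequal observation time, yet provides for it only in the duration model. On its own wording, undischarged patients are non-users.

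A second reply is that period use among all eligible patients is a legitimate descriptive measure. It is, but it mixes the rate of discharge with the choice made at discharge, and variation between providers in the mixture cannot be read as variation in CTO practice.

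A third reply concerns size, and most of it stands. Anyone discharged once in four years has reached a CTO decision, even if later redetained, so the never-discharged share is lower than a per-detention calculation implies. A reader might push the illustration to 10% v 40% undischarged, giving 27% v 18% and an odds ratio of 1.68. The steady-state formula then needs a provider-wide mean stay of 0.40 × 48/0.60 = 32 months, and nothing in the article supports that.

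A reader might also infer that the numerator is wrong because it includes CTOs begun before the window. The article does not support this. Those patients are subject to a CTO during the period, which is the stated outcome, and the stock of older CTOs largely reflects a provider's own use. This merits a sensitivity analysis only.

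**Conclusion.** The point holds as a flaw in the stage 1 analysis set. As written, patients with no discharge from an eligible section in the window count as non-users in a logistic model that makes no stated allowance for time. At equal practice, a provider, legal group or admission year with more undischarged patients shows lower CTO use.

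The direction follows from the article's own definitions. The size does not. It rests on assumed undischarged shares, one detention per patient, and 30% used as a probability per discharge. On those assumptions, 5% v 20% undischarged gives an odds ratio of about 1.26. With short stays the distortion is small: about 0.91 at a 3-month mean stay against full discharge. The time trend arises only if time is represented by admission year, which the article does not specify. It would go too far to conclude that long-stay providers will be materially misranked. The documents show that this can happen, not that it will.

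**What to change.** Restrict the stage 1 model of use to patients with at least one live discharge from a CTO-eligible section within the study period, matching the stage 2 index date. Keep patients who were discharged in the window and later redetained or died. Excluding them because their last detention was open or fatal would remove people for whom a CTO decision had been reached.

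Alternatively, keep all detained patients and model time to CTO with censoring at the end of the window. Discharge without a CTO and death in hospital should then be competing events, and results should be read as cumulative incidence. The rate per detained month would not do: under constant practice it is p/m, that is 0.30/3 = 0.10 at a 3-month mean stay and 0.30/12 = 0.025 at 12 months, so it still reflects length of stay.

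Report the number never discharged by provider, and add a sensitivity analysis counting only CTOs that start at an in-window discharge.

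The cost is one inclusion rule, using care-spell dates that the article says are held, and a somewhat smaller stage 1 denominator. Patients on a carried-over CTO with no in-window discharge also leave the use model; the duration model can retain them.

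### Stage 1 reduces CTO use to one undated ever/never flag per patient over four years, which does not deliver the temporal half of aim 1 and mixes CTO practice with observation time and number of eligible detentions

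*Protocol article*

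**What the plan says.** The first aim in the Introduction is "to examine spatial and temporal variation in the use of CTOs". The Data analysis section repeats this for stage 1: cross-classified multilevel models of all eligible patients "will be used to explore spatial and temporal variation in the use of CTOs". The outcome of the logistic model is then fixed: "CTO use will be considered as a binary outcome (patients subject to a CTO during the study period vs those who were not".

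The window is defined under Data sources and study outcomes: "Four years of MHSDS data will be used covering the period 2011/2012 to 2014/2015, hereafter referred to as the study period".

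The levels are introduced in general terms: "MMs allow variation in outcomes to be apportioned to the appropriate spatial level (eg, between patients, local areas and service settings". The stage 1 model will assess how far "any variation in this outcome is associated with patient, local area and health service characteristics". No year, period, detention or discharge is named as a unit or term for this model.

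A second stage 1 model, for days spent on a CTO, "will include offset variables to take account of different observation times for patients". Nothing equivalent is stated for the binary model.

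Eligibility attaches to a detention: "a patient must be detained in hospital under the MHA on a section that allows for compulsory treatment" (Introduction). The Introduction also gives repeated admission of a small group of patients as one reason for having CTOs, so more than one eligible detention per patient is to be expected.

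**The concern.** The outcome carries no date. A patient placed on a CTO in the first year and one placed on a CTO in the last year have the same value, so the model as written has nothing from which to read a trend in use. Yet a trend in use is half of aim 1.

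The flag also accumulates chances. A patient with three eligible discharges has three occasions to be flagged, and a patient first eligible in 2011/2012 has longer to be flagged than one first eligible in 2014/2015. Variation between providers, areas or patient groups in repeat detention or in observation time can therefore be reported as variation in CTO use, even where the decision at each discharge is made in the same way. The Introduction gives prominence to differences in CTO use between demographic groups and between trusts, and the stage 1 results would be read as evidence on exactly that.

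**Working it through.** The article states no figure for this model, so there is nothing to reproduce. The check is how the flag behaves under known practice.

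**Inputs.** From the documents: a four-year window, and about 30% of eligible patients on CTOs against about 10% originally expected (Introduction). Those are shares of patients, not of discharges; using them as a probability p per eligible discharge is an assumption. Also assumed: independent decisions with constant p (except in step 3), the number of discharges k, the provider mixes, the yearly trend and the re-detention rate r.

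**1. Number of discharges.** P(ever) = 1 − (1 − p)^k.

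| k | p = 0.30 | p = 0.10 |
|---|---|---|
| 1 | 30.0% | 10.0% |
| 2 | 1 − 0.7² = 51.0% | 1 − 0.9² = 19.0% |
| 3 | 1 − 0.7³ = 65.7% | 1 − 0.9³ = 27.1% |

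**2. Two providers with identical practice.** Assume shares of patients with one, two and three discharges of 85/10/5% at provider A and 55/25/20% at provider B, with p = 0.30.

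- A: 0.85 × 0.300 + 0.10 × 0.510 + 0.05 × 0.657 = 33.9%
- B: 0.55 × 0.300 + 0.25 × 0.510 + 0.20 × 0.657 = 42.4%
- Odds ratio: (0.424/0.576) ÷ (0.339/0.661) ≈ 1.4

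With p = 0.10 the same mixes give 0.085 + 0.019 + 0.0136 = 11.8% and 0.055 + 0.0475 + 0.0542 = 15.7%, and the odds ratio is again about 1.4.

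**3. Direction of trend.** For a patient with one eligible discharge in each year and yearly probabilities of 15, 25, 35 and 45%, P(ever) = 1 − 0.85 × 0.75 × 0.65 × 0.55 = 77.2%. Reversing the order gives the same product and the same 77.2%. One discharge every year is an extreme case; it shows the principle, not a typical patient.

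**4. Would year of entry repair it?** Assume constant p = 0.30, a first eligible discharge at mid-year of entry, and further eligible discharges at Poisson rate r per year over the remaining time T (3.5, 2.5, 1.5 and 0.5 years). P(ever) = 1 − (1 − p) × exp(−r × T × p).

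| r per year | 2011/12 | 2012/13 | 2013/14 | 2014/15 |
|---|---|---|---|---|
| 0.2 | 43.3% | 39.8% | 36.0% | 32.1% |
| 0.4 | 54.0% | 48.1% | 41.5% | 34.1% |
| 0.6 | 62.7% | 55.4% | 46.6% | 36.0% |

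Practice is constant, yet every row shows a decline, produced only by shorter remaining observation. With r = 0 each cohort shows 30% and the artefact vanishes.

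**5. With a dated discharge-level outcome**, constant p = 0.30 gives 30% for every provider and year, and the two opposite trends in step 3 are recovered as different trends.

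**The case against.** The strongest reply is that this is a condensed article. It says the stage 1 models will examine temporal variation, the levels are given as examples, and a fuller plan may hold a year term. Calendar time need not sit in the outcome; it can enter as a covariate, and dated spells are available. That stands against the tempting inference that the temporal aim cannot be estimated at all, which the document does not support. It does not remove the point: the outcome is stated, not omitted, and step 4 shows that year of entry on a whole-period flag confounds trend with remaining observation.

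A second reply concerns size. A reader might take 30% as a published rate per discharge, or turn the table in step 1 into odds ratios of 2.4 and 4.5 (two and three discharges against one, at p = 0.30) and read them as the bias between trusts. Neither is supported. The 30% is a share of eligible patients, and those ratios compare individual patients. Independence is also doubtful: CTOs are meant for people with repeated admissions, so higher use among them is partly genuine targeting, and revocation returns a patient to the original order, so later detentions are not clearly fresh decisions.

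Third, a reader might infer that CTOs begun before 2011/2012 are counted. The wording allows this, but stage 1 is restricted to eligible patients and the article does not say whether someone with no eligible detention inside the window is included. It is an ambiguity, not an established error.

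Finally, ever-use per eligible patient is a legitimate descriptive measure and matches the patient-level share in the Introduction. That stands, provided no temporal claim rests on it. Patient characteristics are adjusted for in stage 1, but previous admissions are named only for the stage 2 propensity score.

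**Conclusion.** The point holds as a defect in a stated rule. As defined, the binary outcome does not deliver the temporal half of aim 1, and year of entry alone would not fully repair it wherever patients have repeat eligible detentions. The days-on-CTO model does not fill the gap: its offset adjusts for exposure but gives no calendar trend. Stage 2 matches on index date, but its temporal question concerns CTO effects, not use.

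The flag can also create apparent differences between providers, areas or groups. The size is unknown, because the article gives no distribution of detentions per patient. Under the assumed mixes it is 33.9% v 42.4%, an odds ratio of about 1.4. If nearly all patients have one eligible detention, this distortion is small and a year-of-discharge term would largely suffice, but that term is still not stated.

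The article does not say that repeat detention differs by ethnicity. It therefore does not support the inference that the ethnic differences it reports are an artefact of this kind.

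**What to change.** Make the eligible discharge the level 1 unit, with the outcome being discharge onto a CTO (yes/no). Nest discharges within patient, keep the planned cross-classification by area and provider, add calendar period of discharge as a fixed effect, and let the period effect vary by provider. State that only CTOs starting at an eligible discharge within the study period count; this also settles the ambiguity over earlier CTOs.

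Ever-use per patient can stay as a secondary descriptive measure, with observation time accounted for and no temporal claim attached.

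The cost is a change of wording, one more model level and longer MCMC runs. No new data are needed: the Data sources section says that spell start and end dates are recorded and that patients can be linked across the study period.
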